### Study design

This prospective multicentric (Clinique Victor Hugo-Centre Jean Bernard, Le Mans, France and Centre Hospitalier du Mans, Le Mans, France) study will consist of an 18 month follow-up of a women cohort with breast cancer. Four visits will be scheduled (the study timeline is presented in Fig. 1). Detailed patient assessments will be performed before treatment begins (visit 1: diagnosis); during the week after completion of the first-line treatment, or 6 months after diagnosis, whichever comes first (visit 2); and then 12 and 18 months after diagnosis (visit 3 and 4, respectively). This study has been approved by the French ethics committee of human research CPP SUD EST VI (IDRCB: 2019-A02525–52) and will be performed according to the Declaration of Helsinki. Furthermore, this study protocol has been written in accordance with the SPIRIT guidelines (SPIRIT Checklist provided in Additional file 1) and is registered in a database (ClinicalTrials.gov, NCT04391543, May 2020). In order to longitudinally assess the evolution of biopsychosocial dimensions of CRF, the same procedure will be followed for each visit. Each session will last 1.5 h and will be composed of anthropometric data collection, a semi-structured interview, cognitive tests, postural control tests, neuromuscular fatigability tests and a cardiorespiratory fitness test. Clinical and biological data will be collected during medical follow-ups. In addition, participants will be asked to wear an actigraphy device (received by mail one week prior to each experimental session) and to complete questionnaires to assess psychological aspects and quality of life.

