### Sample size

A sample size of *n* = 200 patients has been chosen on the basis of resource constraints [53]. 200 correspond to a 15% inclusion rate of the patients meeting the inclusion criterion during a 24 months inclusion period and including a 20% potential drop-out rate. Considering this sample size, a sensitivity power analysis performed with G-power (*F* tests family, linear multiple regression, *R*^*2*^ increase) to estimate the smallest effect size we could detect with 90% power regarding our main independent variable (i.e., CRF) at the level of analysis with the lowest power (i.e., level 2, between-person level). This analysis, with a power of 0.90, an α level of 0.05 and 6 predictors (i.e., 6 latent variables), revealed that the smallest effect size we could detect with 90% power, at this level of analysis, is *f*^*2*^ = 0.09, which correspond to a small to medium effect.

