### Statistical analysis

Hypotheses will be addressed by constructing a biopsychosocial model of the relationships among biological, physical, emotional, cognitive and social dimensions of CRF using multilevel SEM. SEM is particularly well-suited to this type of analysis because it simultaneously accounts for multiple interactive relationships among variables, easily handles multiple sources of variance, and permits testing of hypothesized directional relationships [54, 55]. Consequently, the results of SEM analyses facilitate inferences regarding the relationships among variables [56]. Relations between the manifest variables and their underlying latent constructs in a hypothesized biopsychosocial model predicting CRF are presented in Table 3. The model will be tested with the maximum likelihood method using Lavaan *R* package for SEM [57]. A primary cross-sectional analysis will be completed using data collected at each visit, and then subsequently by using the longitudinal data set. The models’ fit was assessed by examining the minimum discrepancy (CMIN/DF), the probability level (*p*-value), the Bentler-Bonett normed fit index (NFI), the comparative fit index (CFI), the Tucker–Lewis-Index (TLI), and the root-mean-square error of approx- imation (RMSEA). A satisfactory model fit is indicated by a CMIN/DF ratio below 2.00 [58], a *p*-value over 0.05 [59], a NFI over 0.95 [60], a TLI over 0.90 [61], a CFI over 0.93 [62], and a RMSEA below 0.05 [63]. All non-significant paths were deleted according to the methods described by MacCallum [64].

**Table 3 Tab3:** Latent and manifest variables included in the model built by SEM

Latent variable	Manifest variable	Test
**Social function**	Family sociability	Semi-structured interview
	Friendly sociability	Semi-structured interview
	Professional sociability	Semi-structured interview
	Income	Semi-structured interview
**Cognitive function**	MoCA total score	MoCA
	TMT time	TMT
	Interference score	Stroop
**Physical function**	95% confidence ellipse area	Postural test
	F_A_	Neuromuscular fatigability test
	VA	Neuromuscular fatigability test
	Db100	Neuromuscular fatigability test
	Power output at LT1	Cardiorespiratory fitness test
	Sleep efficiency	Actigraphy
	Total activity duration	Actigraphy
	Sarcopenia	Abdominal CT at the L3 level
**Biological function**	Cancer stage	Medical file
	Cancer treatment	Medical file
	IL-6 concentration	Blood sample
	IL-1β concentration	Blood sample
	TNFɑ concentration	Blood sample

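### One set of fit cut-offs with no level named is attached to a two-level SEM; four of the six are nearly insensitive to between-person misfit at low to moderate ICC

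*Protocol article*

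**What the plan says.** The Statistical analysis section of the protocol article sets out a model of the "emotional, cognitive and social dimensions of CRF using multilevel SEM", to be fitted by maximum likelihood in lavaan, at each visit separately and then on the longitudinal data. It names six criteria for satisfactory fit: CMIN/DF below 2.00, a chi-square p-value over 0.05, NFI over 0.95, and "a TLI over 0.90 [61], a CFI over 0.93 [62], and a RMSEA below 0.05 [63". No level is attached to any of them, and no separate criterion is given for the longitudinal model. The section also says that all non-significant paths are removed.

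The Study design section fixes the cluster size: "Four visits will be scheduled (the study timeline is presented in Fig. 1". The Sample size section says that the 200 "patients has been chosen on the basis of resource constraints [53", a number "including a 20% potential drop-out rate". It then runs a sensitivity power analysis "at the level of analysis with the lowest power (i.e., level 2, between-person level".

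**The concern.** In a two-level maximum likelihood fit, the usual indices derive from one chi-square that adds the within-person and between-person discrepancies. With four visits, the within-person covariance matrix carries weight 3 per woman and the between-person matrix weight 1. The null-model chi-square behind CFI and TLI is therefore mostly within-person, and RMSEA as software computes it divides by all woman-visits. A well-fitting within-person part can mask a badly fitting between-person part.

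The between-person part answers which women have more CRF and through which dimension. If its factors are ill defined, paths from them to CRF could be reported as part of a well-fitting biopsychosocial model. Path deletion adds to this: at the level with least power, real paths may be non-significant, and removing them would barely move these four indices.

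**Working it through.** **Inputs from the protocol article.** 200 women; 20% drop-out, so 200 × 0.8 = 160 completers; 4 visits; 6 latent and 28 manifest variables (counted from Table 3: 4 social, 3 cognitive, 8 physical, 5 biological, 4 CRF, 4 emotional); the six cut-offs.

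**Assumed, because the article gives no values.** ICC 0.3, 0.5 or 0.7; loadings 0.7 at both levels, or 0.65 within and 0.8 between; factor correlations 0.3, and 0.5 with CRF; normal data; every indicator measured at all four visits.

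**The plan's own figure.** Noncentral F with "6 predictors (i.e., 6 latent variables", df 6 and 193, λ = f² × 200, α = 0.05 and power 0.90 gives f² = 0.090, so the stated 0.09 is reproduced. With 160 completers it is 0.113.

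**Degrees of freedom.** Each level has 28 × 29 / 2 = 406 moments and 28 + 28 + 15 = 71 parameters, so 335 df per level and 670 in all. A one-factor between part has 56 parameters: 350 df at level 2, 685 in all. Cutting CRF off from the other five factors removes 5 correlations: 340 and 675.

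**Formulas.** T = N × [3·F(S_PW, Σ_W) + F(S_B, Σ_W + 4Σ_B)]; CFI = 1 − (T − df)/(T₀ − df₀), with independence at both levels as baseline; RMSEA = √[(T − df)/(df × n)], where n is the number of woman-visits for the whole model and the number of women at level 2.

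**Expected whole-model fit: 200 women, within part correct, between part wrong, loadings 0.7**

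| ICC | Between-person error | CMIN/DF | TLI | CFI | RMSEA | p | NFI |
|---|---|---|---|---|---|---|---|
| 0.3 | one factor instead of six | 1.26 | 0.976 | 0.979 | 0.018 | 5e-6 | 0.904 |
| 0.3 | CRF unrelated to all others | 1.06 | 0.995 | 0.995 | 0.009 | 0.14 | 0.920 |
| 0.5 | one factor instead of six | 1.57 | 0.947 | 0.952 | 0.027 | 9e-20 | 0.879 |
| 0.5 | CRF unrelated to all others | 1.11 | 0.990 | 0.991 | 0.012 | 0.025 | 0.916 |

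**The dilution, at ICC 0.5.**
- One factor: T ≈ 1.57 × 685 = 1,075, an excess of 390 over df. Whole-model RMSEA = √[390/(685 × 800)] = 0.027; level-2 RMSEA = √[390/(350 × 200)] = 0.075. CFI falls from 0.952 to about 0.47.
- CRF unrelated: T ≈ 1.11 × 675 = 749, excess 74. RMSEA is √[74/(675 × 800)] = 0.012 against √[74/(340 × 200)] = 0.033. CFI falls from 0.991 to about 0.90.

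The level-2 values are approximate, since they take the excess from the fit with the within-person model correct.

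**Simulation at these settings** (60 data sets each, 160 and 200 women). The four indices passed together in 97-100% of data sets with a wrong between part. With 200 women, p > 0.05 held in 75% (ICC 0.3) and 80% (ICC 0.5) of data sets for the correct model, 0% for one factor, and 38% and 10% for CRF unrelated. NFI > 0.95 was never met, even by the correct model (mean 0.92 with 200 women).

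**A second simulation** (100 runs per cell, loadings 0.65/0.8, ICC 0.3 and 0.5). Between persons, Physical function was really two factors correlated 0.1 but was fitted as one. All four indices passed in 100% of runs (mean CFI 0.97-0.99, RMSEA 0.012-0.019), while level-2 CFI was 0.82-0.83. The p-value accepted this model in 28-29% of runs at ICC 0.3 and 0-3% at ICC 0.5.

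**Where the four do not all pass.** For one between factor, CFI fails at ICC 0.7 with loadings 0.7 (0.923) and at ICC 0.5 with between loadings 0.8 (0.925). At ICC 0.7 with between loadings 0.8, CMIN/DF (2.71), TLI (0.863) and CFI (0.876) all fail; RMSEA (0.046) still passes. With between-person indicators assigned to wrong factors, CFI failed, yet whole-model RMSEA stayed below 0.05 in 98-100% of runs against a level-2 RMSEA of 0.10-0.13.

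**The case against.** **The article does not say that fit is pooled over levels, and per-level fit may be set out in a fuller document.** True: a reader might infer that pooled fit is prescribed, but that is only the natural result of applying one list to a two-level fit. The point is still more than missing detail, because the article fixes numeric cut-offs for this model and they suit it badly at one level.

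**The full rule does not accept the wrong model.** A reader might infer from the four indices that the plan would certify a wrong between-person structure. It would not: the same sentence also requires p > 0.05 and NFI > 0.95, and no simulated model met all six. But NFI fails right and wrong models alike. The p-value rejects gross misfit, lets milder misfit through fairly often at low ICC, rejects the correct model in 20-25% of data sets with 200 women, and cannot say which level is at fault.

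**The per-visit models would expose the error.** In part. If one factor is fitted there too, CFI is 0.54 and RMSEA 0.116. The merged Physical function gives CFI 0.918 and RMSEA 0.051 at ICC 0.5, both failing, but CFI 0.958 at ICC 0.3. CRF cut off from all other factors still passes the four (CFI 0.945, RMSEA 0.041). A per-visit model also mixes the two levels.

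**The study is not sized on level 2.** Correct. A reader might infer this from the power statement, but the number of women came from resources; only the sensitivity analysis is at that level.

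**Conclusion.** The point holds in limited form. Applied to the overall chi-square, CMIN/DF, TLI, CFI and RMSEA are nearly insensitive to between-person misspecification at low to moderate ICC. For Physical function wrongly merged, or CRF cut off, across ICC 0.3-0.7 and 160 or 200 women, CMIN/DF was 1.05-1.52, TLI and CFI 0.947-0.995 and RMSEA 0.009-0.025, all passing, while level-2 CFI was 0.83-0.95. It does not follow that all four pass whatever the error: gross errors at higher ICC or stronger loadings do fail CFI, and sometimes TLI and CMIN/DF.

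The size rests on assumed ICCs, loadings and correlations. The calculation gives all indicators one common ICC and four visits, whereas CT is taken at two visits only and cancer stage would vary mainly between women. This is a worthwhile, cheap improvement to the plan, not a defect that invalidates it.

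**What to change.** For the longitudinal multilevel model, assess fit by level:

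- Fit the between-person model with the within-person level saturated, and the reverse.
- Report chi-square, CFI, TLI and RMSEA for each level, with the number of women as N at level 2, plus SRMR-within and SRMR-between.
- Show level-2 fit before interpreting between-person paths to CRF, and keep whole-model indices as descriptive.
- Treat the level-2 chi-square and SRMR-between as the main evidence. Do not carry CFI 0.93 over mechanically: at ICC 0.3 the correct model has a mean level-2 CFI of only 0.90-0.93. Level-2 RMSEA is no safeguard alone either (0.033 with CRF cut off at ICC 0.5).

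The level-2 chi-square is the sharper test. For the merged Physical function at ICC 0.3 with 160 women, the expected acceptance of the wrong model falls from 47% to 24%. SRMR-between was not computed here.

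The cost is analysis-plan wording and two extra fits in the software already named, with no new data. The downside is that level-2 indices rest on 160-200 women, so they are noisier and the reported fit may look less favourable.

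### Deleting every non-significant path makes the final CRF model a post-selection result: weak true paths are often lost, and overstated when they survive

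*Protocol article*

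**What the plan says.** The Statistical analysis section starts from a hypothesized model, set out in Table 3, and gives as one reason for using SEM that it "permits testing of hypothesized directional relationships". It then describes the fits: "A primary cross-sectional analysis will be completed using data collected at each visit, and then subsequently by using the longitudinal data set". Model fit is to be judged by a list of cut-offs. The section closes with the trimming rule: "All non-significant paths were deleted according to the methods described by" a cited source. The rule exempts no hypothesized path, and no significance level is given for it.

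Under Study design, "Four visits will be scheduled (the study timeline is presented in Fig. 1"). Under Sample size, the 200 "patients has been chosen on the basis of resource constraints [53"], a number described as "including a 20% potential drop-out rate". The same section gives a sensitivity analysis: with alpha 0.05, power 0.90 and 6 predictors, the smallest detectable effect is f² = 0.09, from an R²-increase F test.

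**The concern.** A model trimmed on its own p-values is the outcome of a search. Its remaining standard errors, p-values and fit indices are computed as though the structure had been fixed beforehand. This has three consequences.

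- A real but weak path is dropped whenever it misses the threshold, and its absence from the diagram looks like evidence that it does not exist.
- A weak path that survives does so because its estimate came out high, so the reported value is too large on average.
- When a path is removed, part of its effect moves to dimensions correlated with it.

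The study asks which biological, physical, emotional, cognitive and social dimensions bear on CRF, and the Discussion hopes for a model usable in practice. These errors bear directly on that answer. If trimming is also repeated visit by visit, chance differences in which paths survive could be taken for the dynamics that the Discussion expects to show.

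**Working it through.** **Inputs.** N = 200, alpha 0.05, power 0.90, 6 predictors and 20% drop-out (Sample size). Four visits (Study design). Five dimensions predicting CRF: Table 3 lists six latent variables, one of which is CRF itself. Completers: 200 × 0.8 = 160. The 0.05 cut-off for deleting paths is my assumption, taken from the Sample size section.

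**The plan's own figure.** For the R²-increase F test, noncentrality is λ = f²N, with df1 = 6 and df2 = 200 − 7 = 193. Power 0.90 gives f² = 0.0900, so the stated 0.09 reproduces. At N = 160, power at f² = 0.09 falls to 0.81. This is a joint test of six predictors, whereas the trimming rule acts on single paths.

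**One path.** With df1 = 1 and five predictors, 90% power needs f² = 0.053 at N = 200 or 0.067 at N = 160. Since r = √(f²/(1 + f²)), this is partial r = 0.22 or 0.25. Below that, whether a path is kept depends increasingly on chance.

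**Retention and inflation.** For a path with partial r, f² = r²/(1 − r²). Retention is the power of the 1-df F test. Inflation is E(|z| given |z| > 1.96)/δ, with δ = √(N f²), by normal approximation. For r = 0.15, f² = 0.0225/0.9775 = 0.0230, so δ = 1.92 at N = 160 and 2.15 at N = 200.

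| Partial r | f² | Kept, N = 160 | Inflation | Kept, N = 200 | Inflation |
|---|---|---|---|---|---|
| 0.10 | 0.010 | 24% | 2.0 | 29% | 1.8 |
| 0.15 | 0.023 | 48% | 1.4 | 57% | 1.3 |
| 0.20 | 0.042 | 73% | 1.2 | 82% | 1.1 |
| 0.25 | 0.067 | 90% | 1.06 | 95% | 1.03 |
| 0.30 | 0.099 | 98% | 1.01 | 99% | 1.00 |

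At N = 160, r = 0.11 gives about 1.8-fold inflation. Hand check at 50% power: δ = 1.96, the mean surviving z is 1.96 + 0.798 = 2.76, and 2.76/1.96 = 1.41.

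**Null paths.** With five truly null paths tested independently, the chance that at least one is kept in a single fit is 1 − 0.95⁵ = 23%.

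**If trimming is done separately at each visit.** Take a constant true effect with power p at every visit. With independent estimates, a mixed keep/drop pattern over four visits has probability 1 − p⁴ − (1 − p)⁴:

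- p = 0.5: 1 − 0.0625 − 0.0625 = 87.5%
- p = 0.3: 75%
- p = 0.6: 84%

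The visits measure the same women, so estimates may be correlated. At p = 0.5, with an assumed equal correlation between visits, the chance of being kept at all four is 6% (correlation 0), 13% (0.25) or 20% (0.5). Being dropped at all four has the same probability. The mixed pattern is therefore 87.5%, 75% or 60%.

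**Simulation.** Backward deletion at p < 0.05 was run with five predictors (mutual correlation 0.3), the same true model at all four visits, N = 160 and 1,500 replicates. R² was 0.33 or 0.56, the range the Background quotes from earlier studies. Within-person correlation was 0 or 0.5.

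- Unequal paths (3:2:1:1:0): the same set survived at all four visits in 1% to 5% of studies at R² = 0.33 and 6% to 11% at R² = 0.56.
- Five equal paths: under 1% at R² = 0.33, but 46% to 48% at R² = 0.56.
- In the unequal case at R² = 0.33, the weakest true paths (standardized 0.114) were kept about 40% of the time, overstated 1.7-fold when kept, and covered by their nominal 95% intervals about 90% of the time. The strongest path (0.343) was inflated by 6%.

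Latent scores were treated as observed, which favours the plan, because measurement error would lower power.

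**The case against.** Several points on the other side stand.

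- **Separate trimming is not stated.** A reader might infer that the structure will certainly change by chance from visit to visit. The documents do not support that: the deletion sentence follows both the cross-sectional and the longitudinal analyses and is tied to neither. Fits at each visit are planned and no common structure is fixed, so the reading is open. If one structure were held across visits, this part would fall away. The Study design sentence beginning "In order to longitudinally assess the evolution of biopsychosocial dimensions of CRF" concerns using the same measurement procedure each time, so it does not settle the matter.
- **Not every surviving path is overstated.** That, too, might be inferred, but at r of 0.30 or more the bias nearly vanishes. The affected paths are small effects: r = 0.15 is f² = 0.023, against the 0.09 that the protocol calls small to medium. No passage says that paths of this size exist.
- **Sole reporting of the trimmed model is not stated.** The article does not say that the full model will go unreported, and the analysis plan is not shown.
- **The cited trimming method cannot be seen.** It may contain safeguards, and neither their presence nor their absence can be assumed.
- **N is not 160 throughout.** Visit 1 precedes follow-up attrition, so N there is nearer 200.

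The study is an observational cohort meant to build a model, so exploratory trimming is legitimate if labelled as such. None of this rescues a rule that removes every non-significant path. Starting from a hypothesized model does not help when hypothesized paths are deleted too.

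**Conclusion.** The post-selection problem holds as the rule is written. It matters for weak paths: at partial r = 0.15, 48% to 57% retention and about 1.4-fold to 1.3-fold overstatement at N = 160 to 200; at r = 0.11 and N = 160, about 1.8-fold. It is negligible from about r = 0.30 upwards. These figures assume a 0.05 deletion threshold and one path among five predictors without measurement error.

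The visit-to-visit consequence is conditional. If trimming is done separately at each visit, a constant path with 50% power shows a mixed pattern in about 60% to 87.5% of studies, for assumed correlations of 0.5 down to 0 between the visit estimates. The protocol should be changed; the change is cheap and affects no data collection.

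**What to change.** Replace the deletion sentence by:

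> All prespecified structural paths are retained in the primary model at every visit and in the longitudinal model, and are reported with estimates and 95% confidence intervals. Any trimmed model is exploratory, labelled as such, and reported with bootstrap selection frequencies. Differences between visits are judged from the estimates and intervals of the common full model, not from which paths survive.

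This costs a short change of text and a bootstrap. The downside is a less parsimonious diagram and a little more analysis. No extra patients, visits or measurements are needed.

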## Discussion

American and European guidelines [65–67] recommend screening for CRF using self-reported questionnaires [68]. Even though this method remains simple and easily feasible for both clinician and patients, this assessment method does not enable the understanding and management of underlying mechanisms. Despite that CRF has been studied for decades, and recent studies have recognized that CRF is multifactorial and may be influenced by a variety of mechanisms [8, 38, 69], few longitudinal and multidimensional studies have been implemented. This is one of the main obstacles to the assessment and management of CRF. Therefore, our longitudinal study is designed to build a model by examining longitudinally biopsychosocial correlates of CRF.

The greatest challenge in designing this study was to select the most pertinent and suitable parameters/variables for each of the biopsychosocial dimensions in order to remain feasible for fragile patients. As it is not possible to measure all parameters potentially involved in CRF, we had to exclude some dimensions such as pain or nutrition that would have otherwise been pertinent [34, 70]. All parameters included are among those most related to CRF, according to the literature.

All patients with localized breast cancer will be included, inherently incorporating various conditions of cancer stages and treatment. Although this may result in a high level of variability and statistical noise, we deemed it necessary to build a real life model that can be later used in clinical practice. Furthermore, with a prevalence up to 50% for CRF [2], it is reasonable to believe that a proportion of participants will not be suffering from clinically important CRF. This could be perceived as a limitation when studying CRF. However, because clinical relevance is based on cut-off values, some patients could potentially be misclassified and we think that CRF should be understood as a continuum. Moreover, even mild CRF can have an impact on patient quality of life.

The BIOCARE FActory study is expected to highlight the dynamics of CRF and its correlates from diagnosis through post-treatment. SEM analysis will hypothesize relations between latent variables (e.g., physical function), assessed through observed variables (e.g., force-time asymptote, voluntary activation) and the CRF variable. Results of the present biopsychosocial model will greatly contribute to a better understanding of CRF and its underlying mechanisms, from diagnosis to the aftermaths of cancer and treatments. They could also be applied to improving interventions for CRF management, notably in supportive care, thanks to a better understanding of CRF mechanisms.

